### Randomization and blinding

#### Randomization method

Participants will be randomly assigned in a 1:1 ratio to receive either antiviral treatment combined with DXP and ropivacaine or antiviral treatment alone, using a computer-generated random sequence created with IBM SPSS Statistics 25.0. The sequence will be stored in numbered opaque envelopes to ensure allocation concealment. The efficacy and safety assessments will be conducted by independent evaluators who are blinded to the group assignments.

#### Blinding method

Due to the nature of the interventions (nerve block vs oral antiviral medication), blinding of patients and treating physicians is not feasible. However, all medication packaging will be standardized by an independent pharmacy service to minimize bias related to treatment allocation guessing. Endpoint assessments for efficacy and safety will be conducted by a dedicated team of clinicians who are blinded to treatment allocation. This team will not be involved in the daily management of the participants.

#### Data handling and analysis blinding

Data collection and entry will be handled by an independent data management team. Statisticians performing the data analysis will remain blinded to treatment group allocations until the database is locked.

### Interventions

#### Control group

Patients in the control group will receive standard antiviral therapy with famciclovir 500 mg, administered three times daily for 7 days, immediately upon recruitment during the viral disease onset (Chen et al., 2014).

#### Intervention group

Patients in the intervention group will receive the same antiviral therapy as the control group. Additionally, they will undergo ultrasound-guided thoracic paravertebral injections. If the patient’s NRS-11 score remains ≥4 2 weeks after the initial intervention, they will receive an additional ultrasound-guided thoracic paravertebral injection. A 5 mL mixture consisting of 0.2% ropivacaine and 4 mg DXP will be injected at each thoracic paravertebral site corresponding to the affected nerves.

We adopted an ultrasound-guided approach for thoracic paravertebral nerve block, as detailed in Pu et al. (2022). The procedure involves a four-step confirmation of the thoracic segment, followed by an in-plane puncture technique. The midpoint of the thoracic inferior articular process and parietal pleura serves as the puncture endpoint. Real-time ultrasound imaging facilitates the accurate placement of the needle tip. A mixture of local anesthetics and corticosteroids is administered for effective neuropathic pain management.

All patients will receive standard pain management, including anticonvulsants, antidepressants, or opioid analgesics, if their NRS-11 score remains ≥4 after treatment (Valladales-Restrepo et al., 2023).

#### Study outcomes

The baseline demographics characteristics of the patients will be collected through searches of the institution’s electronic medical records or direct questioning of the participants. Data collected from the electronic medical records will include gender, age, BMI affected nerves, average weekly consumption of analgesics and levels of inflammatory markers. Data obtained directly from the patients will include pain scores (NRS-11 scores), the Pittsburgh Sleep Quality Index (PSQI), quality of life score, and pain characteristics for comparison with post-intervention outcomes. All patients will undergo systematic follow-up after receiving treatment. The follow-up schedule, outlined in Table 1, is designed to comprehensively assess the long-term outcomes of the treatment. Patients will be followed up at 1, 3, 6, and 12 months post-treatment. These time points were selected based on the natural course of herpes zoster-associated pain and the development of PHN. PHN is typically defined as pain persisting beyond 3 months after the onset of the rash, hence the inclusion of the 3-month mark as a primary time point for assessing PHN incidence (Ahronowitz and Fox, 2018; Ma et al., 2022; Rowbotham and Petersen, 2001). The 1-month and 6-month follow-ups allow for the assessment of intermediate outcomes, such as pain intensity, sleep quality, and inflammatory markers, while the 12-month follow-up provides data on the long-term efficacy and safety of the intervention. The follow-up assessments include the following.

**TABLE 1 T1:** Time schedule of participant enrolment, allocation and assessment.

	Enrolment	Allocation	Post-allocation											Close out
Time point	D0	D0	D1	D2	D3	D4	D5	D6	D7	D14	M1	M3	M6	M12
Enrolment														
Eligibility screening	√													
Informed consent	√													
Allocation		√												
Intervention														
Antiviral therapy			√	√	√	√	√	√	√					
Thoracic Paravertebral Nerve Block Treatment			√							*				
Assessment														
Demographics	√													
Incidence rate of PHN												√	√	√
NRS-11	√	√	√	√	√	√	√	√	√	√	√	√	√	√
Skin lesions	√	√	√	√	√	√	√	√	√	√	√	√	√	√
Pain characteristics and	√	√	√	√	√	√	√	√	√	√	√	√	√	√
SF-12		√							√			√	√	√
PSQI		√							√			√	√	√
Levels of inflammatory markers		√							√			√	√	√
Consumption of analgesics			√	√	√	√	√	√	√	√	√	√	√	√
Adverse events			√	√	√	√	√	√	√	√	√	√	√	√

*If NRS-11 ≥ 4 at D14, a second TPVB, injection may be performed.

PHN: postherpetic neuralgia; NRS-11: The Numeric Rating Scale; SF-12: 12-item Short-Form Health Survey; PSQI: pittsburgh sleep quality index; D: day; W: week; M: month.

#### Primary outcome

Incidence Rate of PHN: PHN is defined as a condition characterized by pain in the dermatomal area that persists for a duration exceeding 3 months following the resolution of the herpetic rash (Kost and Straus, 1996). The incidence rate of PHN will be precisely determined by assessing the percentage of patients who exhibit an NRS-11 score ≥4 during scheduled follow-up visits at 3, 6, and 12 months (patient-reported).

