### Objectives

The primary objective of this trial is to compare the efficacy of DXP combined with ropivacaine versus antiviral treatment alone in preventing ZAP from progressing to PHN within 12 months of follow-up, with the primary evaluation metric being the incidence rate of PHN, defined as a Numeric Rating Scale (NRS-11) score of ≥4 3 months after rash onset.

Secondary objectives include assessing the reduction in pain intensity, improvement in sleep quality (using the Pittsburgh Sleep Quality Index), enhancement of quality of life (using the Short Form Health Survey SF-12), decrease in weekly analgesic consumption, and changes in levels of inflammatory markers (C-Reactive Protein (CRP), Tumor Necrosis Factor-alpha (TNF-α), and Interleukin-6 (IL-6)).

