#### Secondary outcomes

(1) Pain Intensity: This parameter is quantified using the NRS-11, which provides a spectrum ranging from 0, signifying an absence of pain, to 10, indicating the most severe pain conceivable (patient-reported).(2) Sleep Quality: PSQI serves as the instrument to assess the quality of sleep among patients (Buysse et al., 1989) (patient-reported).(3) Quality of Life Score: Patient wellbeing is evaluated using the SF-12, a concise 12-item questionnaire designed to gauge the multifaceted aspects of health-related quality of life (Ware et al., 1996) (patient-reported).(4) Average Weekly Consumption of Analgesics: This metric tracks the mean quantity of each pain-relieving medication consumed on a weekly basis (investigator-reported, based on medical records).(5) Pain Characteristics: Presence of accompanying symptoms such as itching, sensory abnormalities, and hyperalgesia (patient-reported).(6) Levels of Inflammatory Markers: Changes in the levels of inflammatory markers post-treatment, such as CRP, TNF-α, and IL-6 (investigator-reported, based on laboratory tests).(7) Skin lesions: Including the number of days from the initial onset of the rash to its resolution, as well as the largest area of the skin lesion.

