### Comprehensive evaluation

The study’s design, which includes both immediate and follow-up assessments, allows for a comprehensive evaluation of both short-term and long-term outcomes. The primary outcome is the incidence rate of PHN, defined as an NRS-11 score of ≥4 3 months after rash onset. Secondary outcomes include reductions in pain intensity, improvements in sleep quality (using the Pittsburgh Sleep Quality Index), enhancements in quality of life (using the SF-12), decreases in weekly analgesic consumption, and changes in levels of inflammatory markers (CRP, TNF-α, IL-6). If successful, this study could provide a new, effective treatment option for managing ZAP and preventing PHN, significantly improving patient outcomes.

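### The primary endpoint is defined in two ways (3 months from rash onset, or more than 3 months from rash resolution), and the primary test is not tied to one of the three visits

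*Protocol article*

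**What the plan says.** The protocol article describes the primary endpoint in several places.

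- **Objectives:** PHN is "defined as a Numeric Rating Scale (NRS-11) score of ≥4 3 months after rash onset". The same paragraph frames the aim as efficacy "in preventing ZAP from progressing to PHN within 12 months of follow-up".
- **Comprehensive evaluation (Discussion):** the primary outcome is again "defined as an NRS-11 score of ≥4 3 months after rash onset".
- **Study outcomes:** the rationale for the visits also counts from rash onset and gives the 3-month visit primary status. The 6-month visit is described as intermediate and the 12-month visit as long-term. Timing is stated as "Patients will be followed up at 1, 3, 6, and 12 months post-treatment".
- **Primary outcome (under Study outcomes):** PHN is "pain in the dermatomal area that persists for a duration exceeding 3 months following the resolution of the herpetic rash". The next sentence gives the counting rule: "the percentage of patients who exhibit an NRS-11 score ≥4 during scheduled follow-up visits at 3, 6, and 12 months".
- **Table 1:** PHN incidence is ticked at M3, M6 and M12. All visits sit in one schedule after allocation, and the conditional second injection is a D14 entry inside it.
- **Primary outcome (under Statistical analysis):** PHN incidence is compared by a chi-square test, with one relative risk and its 95% confidence interval. No visit is named.
- **Sample size calculation:** one pair of proportions, 34.8% and 16.3%, with α = 0.05 and 90% power. No time point is named.

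**The concern.** Onset and resolution of the rash are different time origins, and pain lasting more than 3 months from one need not have lasted more than 3 months from the other. The section that should settle the primary outcome uses the origin that the Objectives, the visit rationale and the Discussion do not use.

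The visit question is separate. Four readings fit the text: PHN at month 3 only, at any of the three visits, at all three, or three separate comparisons. They do not give the same cases. A patient scoring 5 at month 3 and 2 at month 6 is a case under the first two readings and not under the third.

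The trial is open-label with a patient-reported primary outcome, so its confirmatory claim depends on a primary comparison that is fixed in advance and can be read in only one way.

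**Working it through.** **1. The plan's own sample size.** Inputs from Sample size calculation: p1 = 0.348, p2 = 0.163, α = 0.05 (two-sided assumed, as sidedness is not stated), power 90%, dropout 10%.

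Pooled-variance formula: n = [z(0.975)·√(2·p̄·(1−p̄)) + z(0.90)·√(p1(1−p1) + p2(1−p2))]² / (p1−p2)²

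- p̄ = (0.348 + 0.163)/2 = 0.2555
- first term: 1.960 × √(2 × 0.2555 × 0.7445) = 1.960 × 0.6168 = 1.209
- second term: 1.2816 × √(0.2269 + 0.1364) = 1.2816 × 0.6028 = 0.772
- n = (1.209 + 0.772)² / 0.185² ≈ 3.926 / 0.03423 ≈ 114.7, so 115 evaluable per arm
- with dropout: 115/0.9 = 127.8, so 128; or 115 × 1.1 = 126.5, so 127

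The stated 127 per arm is reproduced. A one-sided test (94 evaluable, 105 with dropout) and a continuity-corrected test (126 and 140) do not match. The plan is therefore sized for one two-proportion test at two-sided 0.05.

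**2. Where month 3 falls on each clock.** The inclusion criteria limit disease duration at entry to two weeks; I take this as counted from rash onset.

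- *Onset clock:* month 3 is 3 months plus 0 to 14 days after onset, about 3.0 to 3.5 months. The visit fits the definition.
- *Resolution clock:* if the rash resolves t weeks after treatment, month 3 is 3 months minus t after resolution. With t assumed to be 0 to 4 weeks, that is about 2 to 3 months, which never exceeds 3 months. Only a rash already resolved before treatment could satisfy the definition at month 3, at up to about 3.5 months. Months 6 and 12 could satisfy it.

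So the definition and the counting rule in the same section disagree at month 3.

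**3. What three tests would cost, if they were run.** Three independent tests at 5%: 1 − 0.95³ = 14.3%. For three equally correlated normal test statistics (simulation, 2,000,000 draws):

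| Assumed correlation | Family-wise error |
|---|---|
| 0 | 14.3% |
| 0.5 | 12.5% |
| 0.7 | 10.9% |
| 0.8 | 9.9% |
| 0.9 | 8.4% |

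The documents give no correlation, so this is a range.

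**4. Effect of each resolution on sample size.** With one test at month 3, N is unchanged: 127 × 0.9 ≈ 114 evaluable per arm gives 89.8% power. If instead each of the three visits could win under Bonferroni (0.05/3 = 0.0167), with the same rates assumed at each visit, the need is 148 evaluable, or 148/0.9 = 164.4, so 165 per arm (330 in total). Power per test at 114 evaluable would be 79.6%.

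**The case against.** The best defence is that the plan is more coherent than it looks. The analysis section describes one chi-square test and one relative risk, the sample size is that of one test, and three places point to 3 months from onset. The resolution wording is a cited disease definition; the rule that does the counting is "NRS-11 score ≥4 during scheduled follow-up visits at 3, 6, and 12 months", which needs no resolution date. The visit used in the test may also be named in an analysis plan that is not shown.

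Much of this stands, and it rules out several stronger readings that a reader might infer:

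- *That patients cannot be classified at month 3.* They can, because the counting rule needs only the NRS-11 score at the visit.
- *That the primary analysis is not a single 5% test.* No section says that three tests will be run or that any one of them may win. The visits could equally form one cumulative endpoint or be descriptive.
- *That the clock starts differently by arm.* Time to rash resolution is a separate secondary outcome ("Including the number of days from the initial onset of the rash to its resolution"), and nothing links it to PHN classification.
- *That the D14 injection moves later visits in one arm.* Table 1 keeps that injection inside one post-allocation schedule, and nothing re-anchors the visits to it.
- *That the definition will be picked once results are known.* Analysts are to stay blinded until database lock, and the month 3 count is the same whichever definitional sentence is kept.

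The defence does not remove the contradiction. An unseen analysis plan can add detail, but the protocol's own primary outcome section would still conflict with its Objectives, and the text would still support more than one primary comparison.

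**Conclusion.** The point holds as an internal contradiction in the primary endpoint that must be corrected. Two time origins are stated, the resolution-based definition does not match its own counting rule at month 3, and the single planned test is not tied to a visit or a combination rule. These conclusions come directly from the text. The clock comparison also assumes that disease duration is counted from rash onset and, for the 2 to 3 month range, that the rash resolves 0 to 4 weeks after treatment.

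The family-wise figure of about 8% to 14% is conditional. It applies only if all three visits were each tested at 5% without adjustment, over assumed correlations from 0.9 down to 0. It measures what the ambiguity leaves open and is not the error rate of the plan as written.

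**What to change.** - Define the primary endpoint once: NRS-11 ≥4 at the month 3 visit, with the 3 months counted from rash onset, as the Objectives and Comprehensive evaluation already do.
- Remove the resolution-based definition from the Primary outcome section under Study outcomes.
- State in both Primary outcome sections that month 3 is the only primary time point, tested once at two-sided 0.05, and that months 6 and 12 are secondary.
- Bring the 12-month phrase in the Objectives and the PHN row of Table 1 into line with this.
- State that visits are timed from allocation in both arms, as Table 1 implies, in place of the post-treatment wording. Given the entry limit, month 3 is then 3 months plus at most two weeks after onset.

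The cost is protocol wording. The visits and the 254 participants are unchanged. Whether the registry entry also needs editing cannot be judged from the document.

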#### Secondary outcomes

(1) Pain Intensity: This parameter is quantified using the NRS-11, which provides a spectrum ranging from 0, signifying an absence of pain, to 10, indicating the most severe pain conceivable (patient-reported).(2) Sleep Quality: PSQI serves as the instrument to assess the quality of sleep among patients (Buysse et al., 1989) (patient-reported).(3) Quality of Life Score: Patient wellbeing is evaluated using the SF-12, a concise 12-item questionnaire designed to gauge the multifaceted aspects of health-related quality of life (Ware et al., 1996) (patient-reported).(4) Average Weekly Consumption of Analgesics: This metric tracks the mean quantity of each pain-relieving medication consumed on a weekly basis (investigator-reported, based on medical records).(5) Pain Characteristics: Presence of accompanying symptoms such as itching, sensory abnormalities, and hyperalgesia (patient-reported).(6) Levels of Inflammatory Markers: Changes in the levels of inflammatory markers post-treatment, such as CRP, TNF-α, and IL-6 (investigator-reported, based on laboratory tests).(7) Skin lesions: Including the number of days from the initial onset of the rash to its resolution, as well as the largest area of the skin lesion.

#### Safety evaluation

Adverse events (AEs) are defined as any unfavorable medical occurrences during the study, irrespective of their relation to the study medication or interventions. All AEs will be meticulously documented and promptly treated. The correlation of AEs with the study interventions will be thoroughly evaluated and reported to the Institutional Review Board (IRB). Study-related AEs will be treated free of charge until recovery. The study will be terminated immediately if any severe AEs result in extended hospitalization or death. The IRB will conduct regular checks on the trial.

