### Exclusion criteria

(1) Special types of HZ infection: Patients with disseminated HZ or HZ at other locations.(2) Puncture risks: Patients with systemic infections, coagulation dysfunction, ongoing anticoagulant/antiplatelet therapy, infections at the puncture site, or thoracic spine abnormalities affecting ultrasound guidance.(3) Special populations: Pregnant or lactating women, individuals with immunodeficiency, severe cardiovascular, cerebrovascular, respiratory diseases, or other serious systemic conditions that impede treatment cooperation, and patients with mental illness.(4) Medication allergies: Patients with allergies to treatment-related drugs (e.g., steroid medications, famciclovir, gabapentin, pregabalin, Nonsteroidal Anti-Inflammatory Drugs (NSAIDs), tramadol) or contraindications for nerve block therapy.

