### Data collection and management

To ensure the accuracy and completeness of the study data, the following data collection and management strategies will be employed.(1) Electronic Case Report Form (eCRF Forms): The eCRF forms will serve as the primary data collection tools for this study, containing clear instructions and annotations. They will be designed to include range and format checks for data entry to minimize errors. Data collection and entry will be handled by two members of the research team, who will not be involved in data analysis, and will perform double-checking. Regular quality control checks will be conducted to ensure data integrity and accuracy. Data analysts will use a blinded dataset for analysis, with blinding maintained until the database is locked.(2) Data Isolation and Confidentiality: Records containing participant names or other identifiable information (e.g., informed consent forms and contact information sheets) will be stored separately from the study data records. Study data will be identified only by participant number and initials to protect privacy.(3) Data Access Control: Data will be stored in password-protected computer systems. Only the Principal Investigator (PI) and authorized research team members will have access to files related to personal data, with all access activities recorded to prevent unauthorized access.(4) Database Management: The final database will be managed by the statistician for subsequent statistical analysis. Before analysis, the data management team will clean and anonymize the data to remove any information that might identify participants.(5) Data Monitoring Committee (DMC) Role: The DMC will periodically review the database to ensure data quality and consistency. The DMC will review the database at key study milestones (after enrolling 30%, 50%, 80%, and 100% of participants) to check for missing, suspicious, and inconsistent data. The DMC will also receive interim results and regularly review safety reports to assess the strength of the evidence and the absolute degree and severity of any safety signals.(6) Special Permissions: Access to the database for personal information retrieval requires special permission, which must be granted by the PI and the DMC. Apart from the PI and the statistician, no one else will have access to the database.

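### As written, a single severe adverse event ending in extended hospitalisation or death stops the whole trial, whether or not it has anything to do with treatment

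*Protocol article*

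**What the plan says.** The stopping rule stands in the protocol article, Safety evaluation: "The study will be terminated immediately if any severe AEs result in extended hospitalization or death". That section opens by defining AEs as "any unfavorable medical occurrences during the study, irrespective of their relation to the study medication or interventions". It also says that the relation of AEs to the interventions will be evaluated and reported to the IRB, and that the IRB will check the trial regularly. The sentence just before the stopping rule is limited to related events: "Study-related AEs will be treated free of charge until recovery". The stopping rule carries no such limit.

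Three other sections bear on it:

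- **Data collection and management, item 5.** The DMC reviews safety reports in order to "assess the strength of the evidence and the absolute degree and severity of any safety signals".
- **Withdrawal criteria, item 2.** An individual with a serious AE is withdrawn if the research team's assessment calls for it. This concerns the participant, not the trial.
- **Study outcomes and Table 1.** AEs are recorded from day 1 to month 12 without distinction by arm, and "the 12-month follow-up provides data on the long-term efficacy and safety of the intervention".

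**The concern.** A trial-level stop should respond to evidence that a study treatment is harmful. This one responds to any qualifying event, including events that carry no information about the injection. Patients are 50 or older with no upper age limit, and half of them receive no injection. A death from an unrelated illness in the control arm at month 11 meets the trigger as fully as a procedural complication would.

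When such an event occurs, the investigators have two options. They can end a 254-patient trial over something that says nothing about the paravertebral injection, or they can carry on and depart from their own protocol text. Neither option protects participants.

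**Working it through.** **1. Reading the rule.** The table sets the sentence against the safeguards that could narrow it.

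| Possible limit | Where it might come from | Does it limit the stop? |
|---|---|---|
| Related events only | AE definition, Safety evaluation | No; it includes unrelated events |
| Causality evaluation | Safety evaluation | Separate sentence, not linked to the stop |
| Intervention arm only | Table 1, AE row | No arm restriction |
| Minimum number of events | Stopping sentence | One is enough |
| DMC weighing of the signal | Data collection and management, item 5 | No role in the stop is stated |
| Judgement by the research team | Withdrawal criteria, item 2 | Individual withdrawal only |

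Nothing in the article narrows the trigger to events that bear on the treatment.

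**2. The number of patients exposed to the rule.** The planned total is 254. With 34.8% versus 16.3%, two-sided α of 0.05, 90% power and pooled variance without continuity correction, the calculation gives 115 per arm. Adding 10% gives 115 × 1.1 = 126.5, so 127 per arm and 254 in total, as the protocol states. (Dividing by 0.9 gives 128.)

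**3. Illustrative chance of a trigger.** The documents give no rate, so r below is an assumed 12-month risk per patient, taken as independent between patients. The chance of at least one event among n patients is 1 − (1 − r)^n.

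| Assumed r | All patients, n = 254 | Control arm alone, n = 127 |
|---|---|---|
| 0.1% | 1 − 0.999^254 = 22% | 12% |
| 0.5% | 1 − 0.995^254 = 72% | 47% |
| 1% | 1 − 0.99^254 = 92% | 72% |

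Even odds among 254 patients come at r = 1 − 0.5^(1/254) = 0.27%. The control-arm column assumes the same risk in both arms. It shows how often an event could arise in patients who never received the injection.

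**4. Effect of dropout.** If the planned 10% contributed no follow-up at all, n would be 254 × 0.9 ≈ 229. The three figures would become 1 − 0.999^229 = 20%, 1 − 0.995^229 = 68% and 1 − 0.99^229 = 90%. Dropout changes little; the assumed rate drives the result.

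**5. Where the true rate may lie.** The exclusion criteria remove patients with "severe cardiovascular, cerebrovascular, respiratory diseases, or other serious systemic conditions that impede treatment cooperation", which favours the low end. The article does not define what counts as extended hospitalisation, and a narrow meaning would lower the rate further. The finding rests on the wording in step 1, not on this table.

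**The case against.** The strongest reply is that caution is appropriate. The Introduction cites one earlier study of this mixture by this route, with 10 patients and no long-term follow-up, so a strict stop can be a legitimate choice. That stands as an argument for a low threshold on events that might be caused by treatment. It does not justify stopping for events that cannot be.

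A second reply is that the preceding sentence concerns study-related AEs, so the authors may have meant the stop to be limited in the same way. That is plausible, but then the limit needs to be written. The section's own AE definition points the other way.

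A third reply is that a journal article leaves reporting procedures, and who takes the decision, to the full protocol. That is fair, and the lack of such detail is not the complaint. The complaint is the breadth of a trigger that the article does state, in mandatory terms.

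A reader might also infer three stronger things that the documents do not support:

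- **That the DMC and IRB are bypassed.** This would be an inference from the word *immediately*. No sentence says that review is skipped, and the article does not set out the order of review and termination.
- **That the trial will probably be stopped.** Every rate above is assumed, and the results run from 22% to 92%.
- **That the stated 90% power would be lost.** That depends on when the stop comes and on whether follow-up of enrolled patients to month 3 also ends. The protocol does not say.

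**Conclusion.** The concern holds as a matter of wording. The protocol fixes a trial-level stop that one severe AE with extended hospitalisation or death sets off, related or not, in either arm. That stop is not connected to the causality evaluation or to the DMC's safety review. It fits badly with the DMC's task of weighing safety signals, although it does not strictly contradict it.

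The size of the problem is unknown. The 22%, 72% and 92% figures illustrate how fast a one-event rule accumulates over 254 patients. They assume 12-month risks of 0.1%, 0.5% and 1%, independence between patients and full follow-up. No test, estimate or sample-size figure in the protocol is wrong because of this sentence. It should still be corrected, because following it could end the trial for a reason that has nothing to do with its question.

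**What to change.** Replace the stopping sentence with:

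> Any death or prolonged hospitalisation, in either arm, is reported promptly to the DMC and IRB. If it is judged possibly related to a study intervention, enrolment and injections are paused until they have reviewed it, and termination is decided after that review. Events judged unrelated do not by themselves stop the study, but the DMC reviews them by arm and can overrule the causality judgement.

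This keeps a quick halt for events that might be due to treatment. It uses the DMC, IRB and causality assessment already in the protocol and needs no additional data collection. The direct cost is a short change of text and ethics approval of the amendment.

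The downside is that the stop becomes less automatic and depends partly on a causality judgement in a trial where "blinding of patients and treating physicians is not feasible". Having the DMC see every such event by arm, with power to overrule, limits that risk without removing it.
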